## Abstract

**Background:**

Manual spinal joint mobilisations and manipulations are widely used treatments in patients with neck and low-back pain. Inter-examiner reliability of passive intervertebral motion assessment of the cervical and lumbar spine, perceived as important for indicating these interventions, is poor within a univariable approach. The diagnostic process as a whole in daily practice in manual therapy has a multivariable character, however, in which the use and interpretation of passive intervertebral motion assessment depend on earlier results from the diagnostic process. To date, the inter-examiner reliability among manual therapists of a multivariable diagnostic decision-making process in patients with neck or low-back pain is unknown.

**Methods:**

This study will be conducted as a repeated-measures design in which 14 pairs of manual therapists independently examine a consecutive series of a planned total of 165 patients with neck or low-back pain presenting in primary care physiotherapy. Primary outcome measure is therapists’ decision about whether or not manual spinal joint mobilisations or manipulations, or both, are indicated in each patient, alone or as part of a multimodal treatment. Therapists will largely be free to conduct the full diagnostic process based on their formulated examination objectives. For each pair of therapists, 2×2 tables will be constructed and reliability for the dichotomous decision will be expressed using Cohen’s kappa. In addition, observed agreement, prevalence of positive decisions, prevalence index, bias index, and specific agreement in positive and negative decisions will be calculated. Univariable logistic regression analysis of concordant decisions will be performed to explore which demographic, professional, or clinical factors contributed to reliability.

**Discussion:**

This study will provide an estimate of the inter-examiner reliability among manual therapists of indicating spinal joint mobilisations or manipulations in patients with neck or low-back pain based on a multivariable diagnostic reasoning and decision-making process, as opposed to reliability of individual tests. As such, it is proposed as an initial step toward the development of an alternative approach to current classification systems and prediction rules for identifying those patients with spinal disorders that may show a better response to manual therapy which can be incorporated in randomised clinical trials. Potential methodological limitations of this study are discussed.

## Background

Neck and low-back pain are common and costly disorders in adult general populations
[1-6]. Manual spinal joint mobilisations and manipulations are widely used treatments in patients with these complaints
[7,8]. Although the underlying mechanisms of these treatments are far from understood, spinal joint mobilisations and manipulations are effective as well as cost-effective in patients with non-specific neck and low-back pain although no more effective than other treatment modalities
[9-14].

Traditionally, manual therapy has a strong focus on the diagnostics, treatment, and evaluation of spinal joint function by emphasising the use of passive physiological and accessory movements
[15-17]. Passive intervertebral motion (PIVM) assessment is used to judge the quantity and quality of functions of spinal motion segments and is assumed to play an important role in diagnostically classifying patients and selecting treatment
[18]. Dutch, New Zealand, and USA manual therapists indeed believe that passive spinal mobility testing is important for deciding on manual mobilisation or manipulation as a treatment option
[19,20]. Moreover, a recent international, multidisciplinary survey showed that PIVM assessment is the most commonly used impairment outcome measure in patients with neck pain
[21].

In order to yield accurate and uniform decisions about treatment options for patients, test results need to be reliable
[22]. Reliability is a component of reproducibility along with agreement and reflects the extent to which test results can diagnostically discriminate between patients despite measurement errors
[23,24]. Agreement, on the other hand, concerns the possibility of examiners to obtain the same test results on different measurement occasions
[25]. Systematic reviews have consistently shown poor inter-examiner reliability for spinal physical tests, and for PIVM assessment in particular
[26-30]. However, the large majority of studies investigating the reliability of physical tests and PIVM assessment can be regarded as test research following a single-test or univariable approach, thus neglecting the multivariable character of the diagnostic process as opposed to diagnostic research
[31].

Physiotherapists conduct a diagnostic process by collecting data through interview and physical examination and by generating hypotheses as to why a problem exists in order to reach a decision about appropriate patient management
[32,33]. During this diagnostic process, manual therapists indeed seem to apply, amongst others, a hypothetico-deductive way of clinical reasoning
[34,35]. PIVM assessment is usually conducted after history-taking, questionnaires, and other physical tests and is indicated after interpreting earlier clinical information and formulating specific hypotheses about spinal joint dysfunction
[35]. Moreover, Canadian manual therapists reported to decide on manual mobilisation or manipulation based on their whole clinical assessment and clinical reasoning in a patient
[36]. It is therefore reasonable to assume that the diagnostic process in manual therapy has a multivariable character.

Over the last three decades, many systems have been developed for classifying patients with spinal disorders, in particular for those with low-back pain
[37]. A systematic review found 28 systems for classifying chronic low-back pain alone and it was concluded that there was insufficient evidence to support or recommend any particular system for use in clinical description, determining prognosis, or predicting response to treatment
[38]. Some systems were tested for their inter-examiner reliability, but evidence was either conflicting or moderate to strong for poor reliability
[27]. On the other hand, using clusters of tests for diagnosing sacroiliac joint dysfunction yielded acceptable reliability
[39-41]. However, the majority of these systems either lack evidence for their reliability, only use certain parts of the clinical examination (e.g. only physical tests), are prescriptive in their application, do not include PIVM assessment, are not related to manual therapy interventions, or do not direct towards treatment decisions. Some systems
[42,43] were developed as treatment-based classification algorithms for subgrouping patients with low-back pain and were strongly based on factors derived from several clinical prediction rules
[44-47]. However, these rules lack validation, and methodological and statistical issues regarding their development have been raised
[48]. In contrast to the field of classification systems for low-back pain, the development and number of systems for classifying neck pain patients lie far behind. Besides a treatment-based classification system for physiotherapy interventions
[49], clinical prediction rules have been derived to identify factors that predict response to spinal manipulation in patients with neck pain but with identical problems as in the rules for low-back pain as mentioned above
[50-55]. In a systematic review, Gemmell and Miller
[56] found poor inter-examiner reliability of multitest regimens using only physical tests for identifying manipulable spinal lesions in chiropractic. Including pain scores and medical history next to manual examination of spinal motion segments resulted in high accuracy in identifying neck pain patients
[57]. To summarise, however, the value of the diagnostic process as a whole to classify patients with neck or low-back pain in order to decide whether or not spinal mobilisations or manipulations are indicated remains unclear.

This is the protocol of a study that aims to determine the inter-examiner reliability among Dutch manual therapists of indicating spinal joint mobilisations or manipulations in patients with neck or low-back pain based on a multivariable, hypothesis-based diagnostic reasoning and decision-making process. Secondly, using univariable logistic regression analysis of concordant decisions about indications, we will explore which demographic, professional, and clinical factors can explain variation in reliability of therapists’ decisions with specific attention to the contribution of PIVM assessment.

## Methods

### Design

This study will be conducted as a repeated-measures design in which pairs of manual therapists independently examine a consecutive series of patients with neck or low-back pain presenting in primary care physiotherapy in the Netherlands. Primary outcome measure is therapists’ decision about whether or not spinal manual therapy (SMT) is indicated in each patient, alone or as part of a multimodal treatment. SMT is defined here as either spinal joint mobilisations or manipulations, or both. Therapists will largely be free to conduct the full diagnostic process as they are routinely used to.

### Participants

Consecutive patients aged 18 years or older presenting with a primary complaint of neck or low-back pain, either referred to primary care physiotherapy by their general practitioner or medical specialist, or by self-referral, will be eligible for participation in the study. Neck pain is defined as pain in the region between the superior nuchal line, the external occipital protuberance, the spines of the scapula, the superior border of the clavicula, and the suprasternal notch, with or without radiation to the head, trunk, or upper limbs
[58]. Patients will not be eligible when headache or dizziness is their dominant complaint. Low-back pain is defined as pain or discomfort localised below the costal margin and above the inferior gluteal folds, with or without radiation to the lower limbs
[59]. All patients who are assumed to have non-specific or (non-serious) specific neck or low-back pain with a potential indication for SMT will be included. Patients who are not able to speak or read Dutch fluently will be ineligible. Patients will receive verbal and written information on all aspects of the study and will be asked to provide written consent at their inclusion. The Central Committee for Research involving Human Subjects (CCMO, the Hague, the Netherlands) decided that a full evaluation of the study protocol by a medical ethical committee was not required because patients will undergo a diagnostic process similar to routine daily practice.

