### Examiners

Examiners will be manual therapists working at least 20 hours a week in their private practices in the Netherlands and registered by the Dutch Association for Manual Therapy or the Royal Dutch Society for Physical Therapy. From a database of those graduated from the Institute for Master Education in Musculoskeletal Therapy (SOMT: Stichting Opleidingen Musculoskeletale Therapie, Amersfoort, the Netherlands), 14 pairs of manual therapists will be invited to participate. Each pair works together in the same practice and practices will be selected based on their ability to logistically organise the study. We aim to include therapists who vary in years of clinical experience in manual therapy. Therapists will attend an information session followed by a two-hour training session in which procedures for digitally registering data are explained and practised. They will not receive additional training in history-taking, physical examination procedures, or using questionnaires. Pairs of therapists will be strictly requested not to discuss their experiences during the study with each other until their last patient has been included. Gender, age, years of clinical experience in manual therapy, highest diploma, practice setting, weekly amount of work related to spinal disorders (hours), teaching experience (yes/no), and participation in research (yes/no) will be recorded as professional characteristics from the participating therapists.

In each practice, a third colleague will function as a research assistant to coordinate the inclusion and flow of patients. Research assistants will be instructed with respect to applying the inclusion criteria, the order of assigning patients to therapists, and assuring blinding procedures.

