### Procedures

From eligible patients, demographic (gender, age, marital status, working status) and clinical (type of complaints (neck or low-back pain), duration of complaints (days), radiation (yes/no), traumatic origin (yes/no), comorbidity (yes/no)) data will be recorded as baseline data by the local research assistant. In addition, baseline pain and disability will be determined using the Numeric Pain Rating Scale (NPRS 0–10, higher scores indicate higher pain intensity), and the Quebec Back Pain Disability Scale (QBPDS 0–100, higher scores indicate higher disability) for low-back pain patients and the Neck Disability Index Dutch Language Version (NDI-DLV 0–50, higher scores indicate higher pain and disability) for neck pain patients, respectively. The NPRS is a reliable and valid scale to measure pain intensity in adults
[60]. The Dutch version of the QBPDS is a reliable and valid instrument for measuring disability in low-back pain patients
[61] and the Dutch version of the NDI is recommended for measuring pain and disability in patients with neck pain
[62].

All baseline data will be available to each therapist before he or she starts the diagnostic process. The first therapist of each pair will be the treating therapist to whom the patient was assigned to, so the order in which both therapists act as the first examiner will vary according to the practice’s planning. The first therapist will screen all consecutive patients with neck or low-back pain for the presence of red flags
[63]. In accordance with guidelines in the Netherlands
[64], patients suspected of having serious (spinal or non-spinal) pathology will not enter the study which will be recorded. Patients will then undergo a full history-taking by the first therapist. The therapist will record his or her findings as well as proposed hypotheses about patient’s health status by formulating explicit objectives for further examination. The therapist will then choose the diagnostic procedures (e.g. observation, physical tests, performance tests, questionnaires) that he or she plans to perform in the patient. After performing each procedure, its outcome will be recorded. If PIVM assessment is indicated, therapists will use three-dimensional coupled movements in flexion and extension directions for each individual motion segment

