[65]. Movements will be judged on mobility (hypermobile-normal-hypomobile), resistance perceived by the therapist during the movement (increased resistance or stiffness yes/no), resistance perceived by the therapist at the end of the movement (end-feel) (increased resistance or stiffness at the end of the movement yes/no), and pain provocation (yes/no). Therapists will perform a maximum of three repetitions for each movement per direction per spinal motion segment to afford the best stiffness discriminability
[66].

The therapist will then be asked to record whether he or she has made any changes to the original examination objectives as well as to specify these changes, and a diagnostic conclusion in terms of specific or non-specific neck or low-back pain is given. Finally, the therapist will make the decision about whether or not SMT is indicated in the patient and, when indicated, it will also be stated whether mobilisations or manipulations, or both, are indicated, and to which spinal motion segments these techniques would be targeted. In addition, the therapist will rate his or her level of certainty of the primary decision about the indication on a bipolar seven-point scale ranging from -3 (completely uncertain) to 3 (completely certain). It will also be recorded which other interventions he or she believes would further be indicated in the patient. However, at this point, no actual treatment will be provided.

After the first therapist has performed the full examination, he or she will leave the examination room and the patient will be given a 10 minute break. After checking whether all data have been registered, the research assistant then guides the second therapist into the room and makes sure that there is no visual or verbal contact between the two therapists. The second therapist will then conduct the full diagnostic process, excluding the screening for red flags, whilst being unaware of the outcomes of the first examination. Patients will be requested not to mention any outcomes or conclusions from the first examination. Both therapists will record all their findings and data into a fit-for-purpose software program. The research assistant will check whether all data have been entered by both therapists.

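### Returning patients are eligible and the blinding covers only the first study examination, so independence is not assured in that subgroup and its effect on kappa is not tracked

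*Protocol article*

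**What the plan says.** **Entry.** Under Participants, the study takes consecutive adults whose main problem is pain in the neck or low back. Those "either referred to primary care physiotherapy by their general practitioner or medical specialist, or by self-referral, will be eligible for participation". The rule is broad: "All patients who are assumed to have non-specific or (non-serious) specific neck or low-back pain with a potential indication for SMT will be included". Three exclusions are stated. Two are under Participants: "Patients will not be eligible when headache or dizziness is their dominant complaint" and "Patients who are not able to speak or read Dutch fluently will be ineligible". The third is under Procedures: "patients suspected of having serious (spinal or non-spinal) pathology will not enter the study which will be recorded". None concerns earlier examination or treatment by either therapist of the pair.

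**Examiners.** "Each pair works together in the same practice" (Examiners). "The first therapist of each pair will be the treating therapist to whom the patient was assigned to" (Procedures), so the order within a pair follows the practice's planning.

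**Blinding.** The second therapist works "whilst being unaware of the outcomes of the first examination" (Procedures). Patients are asked to keep the results of that first examination to themselves. Therapists are asked not to talk with each other about their study experiences until their last patient is in (Examiners). All three safeguards concern the study itself and not care given before it.

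**Recording.** Earlier care is not among the baseline items listed under Procedures or the regression factors listed under Statistical analysis. All baseline data are made available to both therapists before they start.

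**Disclosed limitation.** Potential limitations of this study accepts that same-practice pairs may inflate reliability. Its mitigation is to pair therapists with different levels of experience.

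**The concern.** The design rests on two therapists reaching the SMT decision independently. A patient who returns with a new episode may have been treated before by one of the pair. That therapist may remember the earlier choice. The other may learn of it during a full diagnostic process, because the patient has been asked to stay silent only about today's first examination. The earlier choice hints at what the colleague is likely to decide now.

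Pairing by experience does not reach this route, since it does not affect what is known about an individual patient.

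The result carries weight. Under Statistical analysis, reliability is acceptable if the lower 95% bound of overall kappa reaches 0.60. The Discussion uses the same bound, together with a bias index below 0.10, to support future trials that randomise patients with a positive indication. Failing it leads to a design that needs agreement by two therapists. If agreement in a subgroup partly reflects shared prior knowledge, the reader should be able to see whether the conclusion depends on that subgroup. As planned, no designated item identifies these patients.

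**Working it through.** **1. Inputs.** From Statistical analysis: N = 165, planning kappa 0.70, prevalence 50%, stated half-width 0.109, rule of 0.60 on the lower 95% bound. Not in the documents, and so assumed:
- f, the share of patients in whom both examiners know the earlier decision;
- kappa in those patients: 0.95 if both know;
- kappa in all others: 0.70 (the planning value) or 0.55;
- 50% prevalence in both groups.

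**2. Formula, and the plan's own figure.** With both margins at 50%, chance agreement is p_e = 0.50 and observed agreement is p_o = 0.50 + 0.50κ. Then SE = √[p_o(1 − p_o)/N]/(1 − p_e) = √[(1 − κ²)/N].

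At κ = 0.70 and N = 165: √(0.51/165) = 0.0556, and 1.96 × 0.0556 = 0.109. The stated half-width reproduces. The lower bound is 0.70 − 0.109 = 0.591, so the planning value itself lies just below the 0.60 rule.

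**3. Mixing the two groups.** At equal 50% prevalence kappa is linear in observed agreement, so overall κ = (1 − f)κ_new + f × κ_known. The lower bound is κ − 1.96√[(1 − κ²)/165].

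| κ_new | κ_known | f | overall κ | lower 95% bound |
|---|---|---|---|---|
| 0.70 | – | 0% | 0.70 | 0.591 |
| 0.70 | 0.95 | 10% | 0.725 | 0.62 |
| 0.55 | – | 0% | 0.55 | 0.42 |
| 0.55 | 0.95 | 10% | 0.59 | 0.47 |
| 0.55 | 0.95 | 20% | 0.63 | 0.51 |
| 0.55 | 0.95 | 30% | 0.67 | 0.56 |
| 0.55 | 0.95 | 40% | 0.71 | 0.60 |

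Second row: 0.9 × 0.70 + 0.1 × 0.95 = 0.725; 1.96√[(1 − 0.5256)/165] = 0.105; 0.725 − 0.105 = 0.62.

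**4. Where the rule is crossed.** The lower bound equals 0.60 at an overall kappa of about 0.708. From 0.70 that needs f = (0.708 − 0.70)/0.25, about 3%, or roughly 5 of 165 patients. From 0.55 it needs f = (0.708 − 0.55)/0.40, about 40%.

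**5. The other direction.** If only one examiner knows and kappa in those patients falls to, say, 0.40 (assumed), then from 0.70 the overall kappa is 0.67, 0.64 and 0.61 at shares of 10%, 20% and 30%. The subgroup then lowers the estimate.

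**6. Precision without returners.** If 30% are removed, N is about 115. At κ = 0.70 the half-width is 1.96√(0.51/115), about 0.13, and the lower bound is about 0.57.

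**The case against.** **The article condenses a fuller protocol.** Research assistants are trained in the criteria and the blinding, and rules on earlier contact could sit in those instructions. This cannot be excluded. However, the entry rule and the scope of the blinding are stated affirmatively in the article, and as stated they leave this route open.

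**Earlier care is proper clinical information.** The Discussion wants a picture of decisions in daily practice, returning patients belong to that practice, and a past treatment does not settle the present indication. This stands as an argument against making exclusion compulsory. It does not argue against identifying these patients.

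**The links are possible, not shown.** Nothing says that examiners consult practice records, that patients go back to their former therapist, or that returners are common. This also stands, and it limits the claim to a subgroup of unknown size.

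**Same-practice inflation is already disclosed.** That is true in general terms, but the mitigation given does not act on knowledge of an individual patient.

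**Earlier care may be recoverable.** Therapists record their history findings, so the information may exist in part. It would be incomplete and unstandardised, and it is a weak basis for a prespecified analysis.

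**Conclusion.** The point holds in limited form. Independence is not assured in returning patients, and the plan has no designated item to show whether they affect the result. The effect may be inflation or reduction, and its size depends on a share and on kappas that the documents do not give.

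Under the stated assumptions, the conclusion is sensitive near the planning value: a 10% share in whom both examiners know moves the lower bound from 0.591 to about 0.62. Well below that value it is not: from 0.55, shares of 10% to 30% leave the bound under 0.60 and only about 40% reaches it.

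A reader might infer more: that agreement in the study as a whole no longer reflects independent reasoning, or that kappa will be inflated past the threshold. The documents support neither. Patients not known to the examiners are unaffected, knowledge by both examiners is not shown, and one-sided knowledge can lower kappa. Nor should a point estimate above 0.60 be read as meeting the rule, which concerns the lower bound.

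**What to change.** 1. **Record it.** The research assistant notes at baseline whether either therapist of the pair has examined or treated the patient before for neck or low-back pain, and whether SMT was given. The plan makes all baseline data available to both therapists, so these items need an explicit exception that withholds them.
2. **Widen the instruction.** Under Procedures, also ask patients not to mention earlier care or conclusions by the other examiner.
3. **Prespecify a sensitivity analysis.** Report overall kappa (95% CI) with and without these patients, and state whether the 0.60 conclusion holds in both. Show the change in the point estimate too, because the smaller subset alone lowers the bound.

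The cost is two baseline items, a sentence in the patient instruction and one analysis, with a wider interval in the subset (about ±0.13 at kappa 0.70 if 30% are removed, against ±0.109). The recording does not erase what a therapist remembers; it makes the effect visible.

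The sponsor could instead exclude patients recently seen by either examiner. That narrows the population away from daily practice, slows recruitment of the 12 patients per pair, and leaves older contacts eligible.
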